## Abstract

Effective, patient-tailored rehabilitation to restore upper-limb motor function in severely impaired stroke patients is still missing. If suitably combined and administered in a personalized fashion, neurotechnologies offer a large potential to assist rehabilitative therapies to enhance individual treatment effects. AVANCER (clinicaltrials.gov NCT04448483) is a two-center proof-of-concept trial with an individual based cumulative longitudinal intervention design aiming at reducing upper-limb motor impairment in severely affected stroke patients with the help of multiple neurotechnologies. AVANCER will determine feasibility, safety, and effectivity of this innovative intervention. Thirty chronic stroke patients with a Fugl-Meyer assessment of the upper limb (FM-UE) <20 will be recruited at two centers. All patients will undergo the cumulative personalized intervention within two phases: the first uses an EEG-based brain-computer interface to trigger a variety of patient-tailored movements supported by multi-channel functional electrical stimulation in combination with a hand exoskeleton. This phase will be continued until patients do not improve anymore according to a quantitative threshold based on the FM-UE. The second interventional phase will add non-invasive brain stimulation by means of anodal transcranial direct current stimulation to the motor cortex to the initial approach. Each phase will last for a minimum of 11 sessions. Clinical and multimodal assessments are longitudinally acquired, before the first interventional phase, at the switch to the second interventional phase and at the end of the second interventional phase. The primary outcome measure is the 66-point FM-UE, a significant improvement of at least four points is hypothesized and considered clinically relevant. Several clinical and system neuroscience secondary outcome measures are additionally evaluated. AVANCER aims to provide evidence for a safe, effective, personalized, adjuvant treatment for patients with severe upper-extremity impairment for whom to date there is no efficient treatment available.

## Introduction

Stroke-related disabilities are highly heterogeneous, with frequent occurrence of motor deficits, affecting around 80% of stroke survivors (1). The severity of impairment is diverse, with around 25% of patients showing little to no motor recovery of the upper-limb (2, 3). There is now a bouquet of different types of treatments for upper-limb motor rehabilitation (4–7) ranging from mirror and constrained-induced movement therapy to neurotechnology-based approaches, such as robotics, non-invasive brain stimulation, peripheral nerve stimulation or virtual reality (8, 9). However, most of these therapies may only be applied successfully to subgroups of patients; in particular, treatment strategies for severely impaired patients are limited and non-effective. Specifically, this population may benefit from neurotechnology-based interventions as they will allow these patients personalized, high-intensity and repetitive training (9). Neurotechnologies for stroke motor rehabilitation comprise robot- and exoskeleton-, functional electrical stimulation (FES), brain stimulation- and brain computer interface (BCI)-based interventions. We refer the reader to (5, 8–15) for detailed reviews on the use of these technologies in motor rehabilitation for stroke patients. In addition to the above-mentioned characteristics, these assistive devices are modular, allowing their use singularly or in combination with each other. With the second approach, better results might be achieved due to the potential of synergistic, additive/supra-additive effects of complementary features and interventional targets (8). Robot- and FES-based strategies target the peripheral nervous system by activating muscles, inducing movements and providing sensory feedback. In addition, FES allows for activation of the efferent pathways if used with supra motor threshold amplitudes (16). Brain stimulation and BCI target the central nervous system. The former attempts to modulate the underlying excitability and achieve neuro-plastic effects crucial for learning and reorganization (10, 17, 18); the second one aims to enhance the engagement of the task-specific brain regions to perform the impaired functional tasks. Moreover, the BCI setup orchestrates the other neurotechnologies to reinstate a coherent interaction of efferent and afferent activity essential for behavioral improvement by decoding the recorded brain activity associated with the attempt to move the paretic upper extremity. The peculiarity of BCI is that it allows for functional efferent-afferent contingency, immediate feedback and reinforcement even without any movement capacity (19–21). Albeit promising, BCI as a therapy for upper-limb rehabilitation is still at its infancy and most of the randomized clinical trials (RCTs) are heterogeneous in terms of brain-directed machines used, movements performed, intervention duration and targeted population (13, 22–25). These variabilities are not specific to BCI therapies, but have also been reported in other stroke-related upper-limb rehabilitation treatments (13, 26). As highlighted by the Stroke Recovery and Rehabilitation Roundtables (SRRR) (27, 28) and a recent meta-analysis (29), trials controlled in terms of time point post-stroke and patient phenotype are still lacking. Precision medicine approaches are needed with the clear goal of creating treatment protocols able to adjust the therapy and its specific parameters to the condition and needs of the individual patient to maximize the effects. Meta-analyses have demonstrated a positive effect of dose-response in stroke motor-rehabilitation (30), yet choosing the correct dosage for each patient a-priori remains a challenge (27, 29, 31). Therefore, intervention duration should be individually adjusted along the therapy to allow every patient to achieve the maximum treatment response. Furthermore, the intervention itself may be dynamically adjusted by adding adjuvant treatments. This becomes of relevance when multiple neurotechnologies (or different approaches such as pharmacology) are combined. If each device has a precise target, they should be gradually combined in a patient-tailored fashion to maximize the results; for example starting from peripheral interventions with exoskeleton and FES to allow the training of upper extremity movement, toward a central, orchestrated engagement with the BCI-based approach, followed by further support of non-invasive brain stimulation for neuroplastic and reorganization processes in the large-scale network (32–34).

With the AVANCER (*Accident Vasculaire cérébrale et Apport des Neurotechnologies individualisées chez le patient sévère Chronique: une Etude clinique prospective visant à Restaurer la mobilité du membre supérieur*)^1^ proof-of-concept trial, we propose a personalized neurotechnology-based therapy for upper-limb motor rehabilitation in severe chronic stroke patients. To maximize treatment effects, we propose two main pillars. The first is the combination of neurotechnologies to leverage their synergistic effects. The second is the personalization in the intervention duration and in a therapy assisted by a hierarchical sequence of non-invasive neurotechnologies, i.e., BCI, FES, exoskeleton and transcranial direct current stimulation (tDCS). To acknowledge high-dimensional heterogeneity in the investigated population (e.g., lesion location and dose-response) and because we expect no natural recovery, a within subject design is the most appropriate and has been chosen to evaluate the following hypothesis: the proposed cumulative neurotechnologies-based intervention leads to an increase of at least 4 points on the Fugl-Meyer assessment for the upper extremity (FM-UE) (35) on average across the targeted population, at end of the sequential treatment.

The main objective of AVANCER is to maximize upper-limb motor improvement in severely impaired stroke patients by the end of the cumulative tailored treatment. Secondary aims are to investigate the rehabilitation process in terms of time, intervention, and patients' specifics; and to determine underlying neural and clinically relevant behavioral mechanisms by means of a multi-modal evaluation. Moreover, given the novelty of the protocol, we aim to study the feasibility and safety of this setup and design.

## Methods and Analysis

AVANCER is a sponsor-initiated, national multicenter (Campus Biotech, Geneva and Clinque Romande de Réadaptation, SUVA, Sion, Switzerland) proof-of-concept trial with an individual based cumulative longitudinal intervention design. All recruited patients undergo the intervention.

### Inclusion Criteria

For patients to be recruited in the study, they must fulfill the following requirements: be in a chronic stage and severely impaired. The former means that the stroke must have happened at least 6 months before enrollment; the second is defined by the FM-UE of below 20 points. Specifically, we include patients with limited residual voluntary finger extension measured with the FM-UE score of “hand mass extension” for which we accept a score below or equal to 1. Moreover, patients' MRIs are analyzed to assess that the hand-knob of the lesioned hemisphere is intact. The latter is evaluated case by case as follows: (1) if the stroke lesion does not affect the hand knob area, the hand knob is considered intact; (2) if the stroke lesion affects the hand knob, but the gray matter is not affected, the hand knob is considered intact; (3) if the gray matter of the hand knob area is affected, the hand knob is considered as non-intact and the patient is excluded. A patient is only eligible to participate if he/she understands the protocol and is able to consent. With each patient a cognitive screening with the Montreal Cognitive Assessment (MoCa) (36) is performed. Although there are no well-established cut-off scores due to limited reliability with patients with speech and languages problems, with a score of 18 or lower, upon consent with the patient, contact with the treating physician is made to verify if the patient is capable of understanding the study content. Full inclusion and exclusion criteria are reported in Figure 1.

**Figure 1 F1:**
[figure not shown]
Flowchart of the AVANCER study with patient inclusion/exclusion criteria. The procedure flow shows the timeline with maximum delays between steps in terms of weeks. MoCA, Montreal Cognitive Assessment (36); Bells, Bells cancellation test (37); AST, apraxia screening of TULIA (38); LAST, language screening test for aphasia (39); MI, motricity index (40); NIHSS, NIH Stroke Scale (41); CIRS, Cumulative Illness Rating scale (42); FM-UE, Fugl-Meyer Assessment for the upper limb (35); MAS, modified Ashworth scale (43); MRC, Medical Research Council scale; ARAT, Action Research Arm Test (44); RASP, Rivermead Assessment of Somatosensory Performance (45); TAP, test of attentional performance (subsections of phasic alertness and divided attention) (46); SIS, Stroke Impact Scale 3.0 (47); BDI-II, Beck Depression Inventory scale (48); MFI, Multidimensional Fatigue Inventory (49); PSQI, Pittsburgh sleep quality index (50). sFM-UE is a short version of the FM-UE where the maximum is 54 and reflex items are removed.

### Recruitment

The two study sites (Geneva, Sion) are in continuous contact and close proximity to the respective hospitals (University Hospital of Geneva – HUG; Hôpital Valais de Sion - HVS). Moreover, the project has collaborations with three rehabilitation clinics in the areas (Clinique romande de réadaption – CRR; Berner Klink Montana, Crans-Montana; Clinique La Lignere, Gland). Recruitment is done through multiple channels such as patients' contact through hospitals, study presentation to patients by partnered clinics and leaflets at physicians' cabinets.

### Study Procedure

All thirty planned patients will receive a cumulative neurotechnologies-based intervention: (1) Interventional phase 1 (IP1) uses a BCI to control supra-motor threshold FES for the upper-limb and a hand exoskeleton for flexion and extension of the fingers with arm support; (2) Interventional phase 2 (IP2) adds tDCS to IP1.

The duration of both interventions is tailored for each patient and is determined according to improvement monitored through a short version of the FM-UE (sFM-UE) (35), consisting of 54 points excluding reflexes and coordination items. This short FM-UE is assessed every second session of intervention. The patient is considered to have no further prospect of recovery when no improvement in terms of sFM-UE is seen in the current session (Si), defined by:

(1)
$$\begin{array}{r} {\text{sFMUE}}_{\text{Si}}\;\leq \text{ median}\left({\text{sFMUE}}_{\text{Si}-2},\;{\text{sFMUE}}_{\text{Si}-4},\;{\text{sFMUE}}_{\text{Si}-6}\right) \end{array}$$

When this condition is met, the intervention changes to a second stage and the same procedures take place to determine the end of *IP2*. A minimum of 11 sessions per intervention is provided and equation (1) is thus applied from the eleventh session of both phases. The session counting of *IP1* begins when the patient can govern the BCI (i.e., reaching 70% of accuracy in offline model validation); this choice is made to have a similar amount of *valid* therapy sessions in the two interventional phases. In addition to the therapies, every subject participates in three multimodal assessment visits: before *IP1* (T0), at the change to the second interventional phase (T1), and at the end of *IP2* (T2). A follow-up visit is scheduled 3 months after the end of *IP2*. The full procedure can be seen in Figure 1. Visits and interventions are conducted at the centers, in our laboratory spaces. Only screening and observation visits may be done at the patient's place of residence.

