#### Blinding Procedures

Complete blinding cannot be achieved in this study design (i.e., patients know in which group they have been placed – waiting vs. starting group, though the treatment phase is identical for both groups). The therapist performing the interventions is blinded to the scores given at the evaluation visits by the assessor. Within the protocol, there is at least one trained therapist per study site. The therapist assigned to one study site performs the intervention and assesses the sFM-UE for all patients belonging to the same site. An assessor, not involved in any way in the treatment (i.e., blinded to therapies' outcomes and sFM-UE) conducts the assessments at the full evaluation visits (T0, T1, and T2). The therapist of one site takes the assessor role for the other site for the clinical measures.

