### Primary and Secondary Outcome Measures

The primary outcome measure is the change in the 66-point FM-UE. The null hypothesis will be rejected when a statistically significant improvement between pre-intervention (T0) and the end of the cumulative treatment (T2) of at least 4 points is found. A medically clinically improvement difference (MCID) lower than the commonly used 5.25 point was chosen based on three current studies addressing the MCID (59–61). The three studies involve different stroke subgroups: chronic and moderately impaired (59), subacute and moderately impaired (60), and subacute and severely-to-moderately impaired (61). As suggested by (60), being in the chronic state makes the MCID drop significantly (5 vs. 9–11 points) and further reduction (around 2 points) is observed with severity. A lower MCID is also supported by (62) that suggests a decrease in the standard error in the reliability and validity of the FM-UE with severely affected subjects as there are less uncertainties when no movement can be performed.

Secondary outcomes look at the effectiveness of the two interventional phases separately and at the general benefit of the rehabilitation compared with the natural course determined from the waiting group; the latter is expected to be negligible in the chronic state. This comparison will be done through the clinical scales evaluated during the observational period of the waiting group. To evaluate if the recovery is long-lasting, all patients will be assessed on clinical scales (including FM-UE) 3-months after T2. Moreover, to study the underlying mechanisms of motor recovery during treatment, we will base our analyses on longitudinal multi-modal assessments data: motor and cognitive scales scores will be evaluated together with neural correlates from neuroimaging techniques including MRI and a combination of electrophysiological measures, as detailed above. Secondary outcomes also include safety, feasibility, and tolerability of the experiment.

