### Statistics

To evaluate if significant motor improvement of the upper-limb is achieved, the FM-UE scores of all the 30 patients will be compared between the final (T2) and the initial (T0) evaluation visits: we will use a two-tail paired Wilcoxon Signed Rank test, with the probability value set at 0.05. The null hypothesis is H0 = “FM-UE scores at T2 and FM-UE scores at T0 follow the same distribution”, H1 = “FM-UE scores at T2 do not follow the same distributions of scores at T0; the distributions are significantly different”. H0 will be rejected if a *p-*value < 0.05 is obtained. This evaluation will be considered together with the expected four-point improvement on average.

To assess if the observed changes in the FM-UE are long-lasting, we will compare with the same test (Wilcoxon Signed Rank, alpha = 0.05) the FM-UE scores at T2 with those acquired at the follow-up (3 months after T2). Another related secondary outcome regards the validation of motor function stability of chronic stroke patients (i.e., no FM-UE improvement during the observation period). We will use a Kruskal-Wallis test with alpha at 0.05 to investigate differences in the FM-UE scores at the three time points of the observation period. We do not expect to reject the null hypothesis for which the three groups are said to come from the same distribution.

Among the most important secondary outcomes is safety and feasibility; for these, descriptive statistics will be provided. One major safety outcome is incidence of epileptic seizures during the intervention period with tDCS, as well as other SAEs. Furthermore, feasibility will be determined by the drop-out rate, usually in clinical trials set to up to 20%.

Important exploratory analyses will focus on the difference between the two interventional phases; such investigation might give an insight on the role of tDCS in the rehabilitation. To test the effect of dose and intervention type on the FM-UE we will use a mixed effects linear model with random effect of subject and fixed effects of session, intervention type and the interaction of the two. If significant results will be observed, we can then build on this initial model by adding more independent variables such as lesion location and time post-stroke. Other analyses will correlate the multimodal data acquired during the three full evaluations (T0, T1, T2), such as corticospinal tract integrity and the TMS evoked potential, with the clinical scales.

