Statistical analyses will be performed in a per protocol way using only the data of patients who have finished the study protocol (i.e., drop-out and excluded patients will not be included in the main analyses).

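### Because the sFM-UE decides how long each phase lasts, the planned mixed model with only a random subject effect can show a session-by-phase interaction with no tDCS effect

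*Protocol article*

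**What the plan says.** Study Procedure sets the length of both phases from the short Fugl-Meyer score, taken every second session: "The patient is considered to have no further prospect of recovery when no improvement in terms of sFM-UE is seen in the current session (Si"). Equation (1) defines this as a current score no higher than the median of the scores two, four and six sessions earlier. On timing, "A minimum of 11 sessions per intervention is provided and equation (1) is thus applied from the eleventh session of both phases". All patients go through the phases in the same order, IP1 and then IP2 (IP1 plus tDCS).

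Primary and Secondary Outcome Measures states: "Secondary outcomes look at the effectiveness of the two interventional phases separately". Statistics places the phase difference among the exploratory analyses and says that "such investigation might give an insight on the role of tDCS in the rehabilitation". The model is a "mixed effects linear model with random effect of subject and fixed effects of session, intervention type and the interaction of the two", with the FM-UE as outcome. Analyses are per protocol, "using only the data of patients who have finished the study protocol".

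The Introduction justifies the within-subject design by heterogeneity between patients and gives dose-response as one example. That amounts to expecting improvement per session to differ between patients. No size is given.

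**The concern.** The outcome being modelled also decides how many sessions each patient contributes. Patients who improve quickly stay longer in each phase, so the late sessions of IP1 and IP2 come mainly from them.

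A random intercept gives each patient one level for the whole study. For a steep improver that level is too high for the IP1 scores and too low for the IP2 scores. Because steep improvers dominate the late sessions, the IP1 slope is pulled down and the IP2 slope up. The difference lands in the session-by-phase interaction, which is the term that would carry any insight into tDCS. The error favours the tDCS phase. Statistics also proposes to build on this model with further covariates if it gives significant results, so a false signal would be carried forward.

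**Working it through.** The article gives no operating characteristics for equation (1) or for the mixed model, so there is no figure of its own to reproduce.

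**Inputs from the article.** 30 completers; scores every second session; first check at session 11; the same rule in both phases; the model as stated. The hypothesised programme "leads to an increase of at least 4 points on the Fugl-Meyer assessment for the upper extremity (FM-UE) (35) on average".

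**Assumptions.** Mean slope 4/22 = 0.18 per session (the 4-point target applied to the sFM-UE over 11 + 11 sessions); straight-line courses; whole-point scores; between-patient slope SD 0 to 0.18; rating-error SD 0.5 to 3; a cap of 21 or 61 sessions per phase (the article gives no maximum); no tDCS effect.

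**Step 1: the rule selects on slope.** In a series that never falls, median(S[i-2], S[i-4], S[i-6]) = S[i-4], so the rule fires when no whole point was gained over four sessions. Simulated probability of meeting it at session 11, for error SD 0.5 to 3:

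- true plateau: 0.56 to 0.77;
- 0.18 per session: 0.37 to 0.47;
- twice that rate: 0.09 to 0.40.

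**Step 2: why one intercept is not enough.** Take a patient whose slope is 0.18 above the mean, with 21 + 21 sessions (mean session 21.5). Around the patient's own level, the deviation from the common line is 0.18 × (11 − 21.5) = −1.9 in mid-IP1 and 0.18 × (32 − 21.5) = +1.9 in mid-IP2. A flat patient with 11 + 11 sessions (mean session 11.5) has −0.18 × (6 − 11.5) = +1.0 and −0.18 × (17 − 11.5) = −1.0, and contributes nothing after session 11 of a phase.

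**Step 3: size.** Random-intercept model, cumulative session count. Each cell is the mean false interaction (IP2 slope minus IP1 slope, per session) and the share of trials with p<0.05.

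| Slope SD | Cap | Error SD 0.5 | Error SD 1 | Error SD 2 | Error SD 3 |
|---|---|---|---|---|---|
| 0 | 61 | 0.00, 6% | 0.00, 4% | 0.00, 6% | 0.00, 4% |
| 0.045 | 61 | +0.03, 57% | +0.01, 10% | +0.01, 7% | 0.00, 7% |
| 0.09 | 21 | +0.08, 98% | +0.05, 50% | +0.03, 10% | not run |
| 0.09 | 61 | +0.08, 100% | +0.06, 61% | +0.03, 13% | +0.02, 8% |
| 0.18 | 21 | +0.19, 100% | +0.16, 98% | +0.10, 47-52% | not run |
| 0.18 | 61 | +0.11, 100% | +0.17, 99% | +0.11, 58% | +0.08, 26% |

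Counting sessions within phase, at error SD 1 and cap 61, gives +0.07 (56%) at slope SD 0.09 and +0.32 (94%) at slope SD 0.18.

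**Step 4: controls.** With phases fixed at 13 sessions the same model gives 0.00 and 0-5%; fixed 11 + 11 sessions gives about 2%. The false signal therefore needs outcome-dependent length as well as the single intercept. Keeping the rule and adding a random slope of session gives about 0.00 and 3-8% at error SD 1. In one set of 120 trials per setting with slope SD 0.75 × 0.18 = 0.14, the random-slope model rejected in 5.8% against 90% for the intercept model on the same data (error SD 1), and in 5.0% against 27.5% (error SD 2).

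**Step 5: limit.** If one recovery course saturates across both phases (time constant 6 sessions, total gain 4, SD 2), every version gives −0.16 to −0.24 per session with no tDCS effect. Saturating courses also give a negative interaction under fixed-length phases, so this comes from time and fixed order, not from the rule.

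**The case against.** **The reading of the model.** The article says neither 'only' nor 'intercept', and covariance structure and session coding are commonly left to an analysis plan. A random slope would fit the wording. This limits the claim, but a random effect of subject, with nothing further, ordinarily means an intercept, and the model so stated has the defect.

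**The outcome.** Statistics names the FM-UE, which is scored at evaluation visits. The session-level score is the sFM-UE, rated by the therapist who "performs the intervention and assesses the sFM-UE for all patients belonging to the same site". This matters. With FM-UE change per phase regressed on sessions in that phase, a check gave a mean interaction of −0.015 to +0.031 and p<0.05 in 3-9%, so essentially no false signal. With raw FM-UE at T0, T1 and T2 on cumulative sessions, the upward pull remains. The point is therefore tied to the session-level reading, which a fixed effect of session suggests but the article does not settle.

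**Assumed sizes and direction.** Slope variation, rating error and linearity are all assumed, and some settings are near nominal. A course saturating across both phases reverses the sign. Both objections stand as limits on size and direction.

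**Stronger readings.** A reader might infer that the rule's description of a patient without further prospects must be reworded. Study Procedure, however, defines that term by equation (1), and the Abstract refers to a quantitative threshold. A reader might also infer that the plan credits the T1-T2 gain to tDCS. No section says so; Statistics offers only a possible insight, under an exploratory label.

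**Conclusion.** The point holds in a narrow form and is minor. The exploratory mixed model, read as a random subject intercept and fitted to session-level sFM-UE scores, can produce a positive session-by-phase interaction from the stopping rule alone when slopes differ between patients, as the Introduction expects.

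At error SD 1, cumulative counting and straight-line recovery, the false interaction is about +0.05 per session at slope SD 0.09 and about +0.16 at slope SD 0.18. Against the target rate these are 0.05/0.18 = 28% and 0.16/0.18 = 89%. The problem disappears or nearly so with equal slopes and cumulative counting, with small slope variation unless rating error is also small, or with rating error large relative to the slope variation. Confidence in the size is medium, because none of these quantities is in the article.

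The result does not mean that any observed interaction would be false or would always be positive. The T0-T2 Wilcoxon test does not use this model and is unaffected.

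**What to change.** In Statistics, add a random slope of session per subject to the mixed model, and state that the session-level outcome is the sFM-UE. This costs one model term and one clarifying phrase, with no extra data and no patient burden. In the simulations the interval for the interaction was no wider than without the random slope. The correction relies on roughly straight-line courses.

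Optionally, as a sensitivity analysis only, estimate one sFM-UE slope per patient and phase over sessions 5 to 11 and report the paired difference with a 95% interval. Every completer has these scores, and that phase's own stop does not select them. In the simulations it gave 0.00 and 3-7%. Its intervals are about 2.5 to 3 times as wide as those of the all-session model (half-width about 0.07, 0.12 and 0.24 per session at error SD 0.5, 1 and 2), and it drops the later dose range, so it should not replace the mixed model.

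Neither analysis separates tDCS from time or fixed phase order, and the report should say so beside the result. No change is needed to the wording of Study Procedure or of Primary and Secondary Outcome Measures.
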